**Methods and design:**

We plan to recruit 150 women with POI from four participating hospitals in China. Participants will be randomized in a 1:1 to receive oral BSHX or BSHX placebo. All participants will be treated for 3 months and will be followed up for another 3 month. The primary outcome is questionnaire scores based on the changes in the total symptoms, which is the Chinese version of the Menopause-Specific Quality of Life (CMS) (Nie G, Yang H, Liu J, Zhao C, Wang X, Menopause 24(5):546–554, 2017). CMS will be measured before the intervention, at 3 months and 6 months after randomization for all participants. The other measurements include serum sex hormone levels, anti-Müllerian hormone (AMH) levels, ovarian peak systolic velocity (PSV; cm/s), and antral follicle count (AFC). In this study, the regulatory effects of traditional Chinese medicine on hormones were evaluated by the changes of serum sex hormone levels, which include serum estradiol (E2), luteinizing hormone (LH), and follicle-stimulating hormone (FSH). These indicators will be measured before intervention and at 3 months after randomization.

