### Removal, dropout, suspension, and termination criteria

During the clinical trial, participants who violate the protocol operation will be removed their participation, for instance, failed to take the drug in accordance with the regulations (medication compliance less than 80%) that affect the judgment of drug efficacy because incomplete data will affect the judgment of efficacy and safety. Participants can voluntarily drop out at any time during the trial. Emergency unblinding or loss of eligible subjects to follow-up will be considered dropping out. If the participant drops out, the last recorded data will be recorded and analyzed. These will be recorded in detail in electronic medical records. If participants have any of the following circumstances, the drug treatment discontinues immediately, while safety or post-treatment visits may continue. These circumstances were (1) a serious adverse event occurred, (2) pregnancy, (3) use of medication that can affect menstrual cycle or ovarian function, (4) the participant withdrew the informed consent form, and (5) the subjects showed hypersensitivity reactions to BSHX, such as stomach pain and diarrhea. Once the blindness is made public, or the opening rate of emergency letters exceeds 20% of the sample size, it means that the double-blind experiment will be invalidated and the entire study will be terminated.

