### Follow-up

All included patients will be re-evaluated at 2, 4, 6, 8, 10, 12, 16, 20, and 24 weeks’ follow-ups. Wherever in-person follow-up was not possible, video conferencing or telephone follow-up was carried out.

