### Safety assessments

Studied medicine safety testing includes liver and renal function test, blood routine examination, urine routine examination, stool routine examination, and electrocardiogram. These parameters will be obtained both at screening and after treatment, and all samples were tested by the Jiangsu Province Hospital on Integration of Chinese and Western Medicine in China. Standardized protocols exist at the study center regarding the management of known of potential adverse effects. Adverse events related to the intervention will be monitored through review of the patient’s records, participant self-report, and by the clinicians. All adverse events during treatment and follow-up will be recorded and analyzed in detail. If a participant has a serious adverse event and was not safe to continue the trial, the participants were requested to withdraw from the trial. Immediate relevant treatments were provided to those participants, and following up continued until the response was terminated.

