### Statistical analysis

Data will be analyzed with SPSS V.21 (IBM) by statisticians independent from involved researchers in this study. Efficacy and safety will be evaluated by intention-to-treat (ITT) analysis within the full analysis set (FAS) according to the ITT principle. At the same time, per-protocol (PP) analysis will apply to evaluate data collected from subjects who have completed all steps of the trial protocol. Results of the full analysis set and the per-protocol set will be compared. All prespecified outcomes will analyze in the ITT population because ITT analysis often underestimates the efficacy and was usually conservative. On the contrary, PP analysis overestimates the efficacy and the differences between the two groups. Therefore, this study mainly uses ITT analysis, and PP analysis will be applied if there was a statistical significance. Various assignment methods were used to detect whether the results of different assumptions of missing data are robust. The safety evaluation will be conducted by ITT analysis.

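### Visits after a drug stop or unblinding are not required, so the primary CMS score can be lost for women still under consent, against the plan's ITT analysis; the likely bias is small

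*Protocol article*

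**What the plan says.** All references are to the protocol article.

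- **Removal, dropout, suspension, and termination criteria.** There are five reasons for stopping drug: a serious adverse event, pregnancy, a drug that can affect the cycle or ovarian function, withdrawn consent, and hypersensitivity. After any of them, "the drug treatment discontinues immediately, while safety or post-treatment visits may continue". The same section says "Emergency unblinding or loss of eligible subjects to follow-up will be considered dropping out", and "If the participant drops out, the last recorded data will be recorded and analyzed".
- **Randomization and blinding.** After a serious adverse event or an emergency unblinding event, the code is opened at once.
- **Safety assessments.** A woman with a serious adverse event who cannot safely go on is asked to withdraw from the trial. She is treated, and "following up continued until the response was terminated".
- **Abstract, Methods and design.** "CMS will be measured before the intervention, at 3 months and 6 months after randomization for all participants".
- **Follow-up.** "All included patients will be re-evaluated at 2, 4, 6, 8, 10, 12, 16, 20, and 24 weeks"; where a visit in person was not possible, "video conferencing or telephone follow-up was carried out".
- **Statistical analysis.** "this study mainly uses ITT analysis", within a full analysis set that the article does not define. CMS is compared between arms at month 0 and month 3. Several ways of filling in missing data are to be used as a robustness check.

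**The concern.** An ITT comparison needs the month-3 score of every randomized woman, on drug or off it. The abstract and the follow-up section promise that score for everyone. The stopping rule does not secure it: it leaves later visits optional for all five reasons, although only withdrawn consent makes that unavoidable.

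For a serious adverse event the rules go a step further. The blind is broken, emergency unblinding counts as dropping out, and a dropout is analyzed on her last recorded data. Read together, these can turn such a woman into a dropout even if she misses no visit.

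CMS is the primary outcome. Stops may also differ by arm: the hypersensitivity reason is worded around BSHX, and women on placebo whose symptoms persist may be more likely to start another hormonally active drug. An imbalance of the first kind would usually shrink the observed difference, and one of the second kind would enlarge it. Sensitivity analyses can vary the assumptions about scores that were not collected, but cannot recover them.

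**Working it through.** The plan gives no figure for stops or lapsed visits, so there is none to reproduce. The check first traces the rules and then sizes the effect under stated assumptions.

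**Tracing one woman.** She stops drug at week 5 because of a reaction and has not withdrawn consent.
1. Later visits are allowed but not required.
2. If they lapse, she is lost to follow-up and so counts as a dropout.
3. Her last recorded data are analyzed. The visits at weeks 2 to 10 have no stated CMS, so on the text shown her last CMS is the baseline one.
4. In a month-0 to month-3 comparison she has a change of zero, or no value if the full analysis set needs a post-baseline score.

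**Inputs from the sample size section.** Planned difference 2.9 points; SD 7.42; 150 women; maximum drop-out 15%. Allocation is 1:1, so there are 75 per arm. The drop-out ceiling is 0.15 × 75 = 11.25, about 11 women per arm.

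**Assumptions (not in the documents).**
- *k*: excess of women in one arm who stop before month 3, lapse and are entered at baseline. Taken as 5, for example 11 v 6.
- *c*: mean placebo improvement in CMS. Taken as 0 to 2.9 points.
- *r*: share of the 2.9-point drug benefit kept after an early stop. Taken as 0 in the main case and 1 at the extreme.

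**Standard error of the difference.** 7.42 × √(2/75) = 1.21 points.

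**Main case, r = 0.** Each such woman would have scored a change of *c* but is entered as 0. With 11 v 6, the difference shifts by (11c − 6c)/75 = 5c/75, so only the excess matters.
- c = 0: shift 0.
- c = 2.9: 5 × 2.9/75 = 0.19 points. That is 0.193/2.9 = 6.7% of the planned effect and 0.193/1.212 = 0.16 standard errors.

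An excess in the BSHX arm lowers the difference by this amount. The same excess in the placebo arm raises it by 5c/75, again 0 to 0.19 points.

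**Extreme case, r = 1.** For 5 v 0 the shift is 5(c + 2.9)/75: 0.19 points at c = 0 and 5 × 5.8/75 = 0.39 points (13.3% of 2.9) at c = 2.9. When r is above 0, the number of stops on BSHX matters as well as the excess: 11 v 6 at c = 2.9 gives (11 × 5.8 − 6 × 2.9)/75 = 0.62 points. That would need women who left early to keep the full benefit of a 3-month course and the whole drop-out ceiling on BSHX to arise in this way, so it is not a likely size.

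**If the month-3 CMS is collected from these women and used, the shift is nil.** If they are instead excluded from the full analysis set, the bias depends on how they differ from the women who remain; the documents give nothing to size that.

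**The case against.** The best defense is that the protocol already follows everyone. The follow-up section covers all included patients to week 24 and allows remote contact, the abstract promises CMS for all participants, and neither exempts women off drug. The stopping rule separates stopping drug from stopping visits, which is sound, and its permissive verb may be there only because withdrawn consent is on the list. This shows the likely intention. But the sentence that sites would apply to a woman who stops drug is the permissive one, and it covers the other four reasons too.

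Three stronger readings are tempting, and the document does not support them.
- *That early stoppers are certain to enter at baseline.* The last-recorded-data rule does not name carry-forward, the full analysis set is undefined here, and the data collection schedule (Table S4) is not shown and could include a CMS at early termination. Zero change is the natural reading, not a stated rule.
- *That follow-up after a serious adverse event ends when the event resolves.* The safety section does not say so; its sentence can be read as a minimum for safety follow-up. The fault is that nothing ties it to month 3 or month 6.
- *That the whole 15% drop-out allowance measures this problem.* That ceiling covers every cause, including voluntary dropout and withdrawn consent, which a change to this sentence cannot reach.

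Two further points stand. The effect needs an early stop, a lapse despite remote contact, a substituted or excluded score, and imbalance by arm, all together. And a menopause symptom score from a pregnant woman is hard to interpret. That is a reason to say how it will be handled, not a reason to leave it uncollected.

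**Conclusion.** The point holds as an inconsistency in the protocol. The rules for drug stops and unblinding do not secure the primary outcome for women still under consent, while three other parts of the article assume that it will be there. Where a score is lost, either likely handling departs from ITT.

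The size is small: 0 to 0.19 points of the planned 2.9, at most 0.16 standard errors, in either direction. This rests on an assumed excess of 5 of 75, a placebo improvement of at most 2.9 points and no benefit kept after an early stop; none of these comes from the documents. It would not by itself overturn a clear result. It is worth correcting because it touches the primary outcome and the remedy is cheap.

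**What to change.** 1. In the removal and dropout section, state that women who stop study drug or are unblinded, for any reason other than withdrawn consent, complete the month-3 and month-6 CMS, by telephone or video if needed, and are analyzed in their randomized arm.
2. In the safety section, state that following a serious adverse event until it resolves is in addition to these two assessments.
3. Do not use a carried-forward baseline as the main analysis value for a missing month-3 CMS. Keep it at most as one of the missing-data sensitivity analyses already planned. This also covers women whom the first two changes cannot reach.

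The cost is a few reworded sentences and modest effort to follow women who are off drug, at visits that are already scheduled. The trial status section expected follow-up to end by late November 2021, so the first two changes help only where visits are still open. The third can be made at any time before unblinded analysis.

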### Randomization and blinding

The randomization sequence is generated by a computer and randomization numbers are hidden in sealed, opaque, and sequentially numbered envelopes, which are properly kept until the end of the trial. Participants will be randomly assigned (1:1) using a computer-generated randomization sequence to receive oral BSHX or BSHX placebo. The statistician who is not involved in recruiting will prepare the randomization list, and the list will not be available to anyone in any center. Researchers who do not participate in the recruitment label the envelopes. Meanwhile the size, color, taste, and shape of the placebo are consistent with the corresponding drugs, and all study groups assigned by different numbers will use the same packages of medicines. All the documents related to the randomization and allocation sequence generation will be kept in a box in a locked cabinet away from the clinical environments. Packages of BSHX and placebo were provided to randomly assigned two groups of women in each hospital’s centers. This is a double-blind trial, in which all researchers and subjects will be blinded for the treatment allocation until the trial is completed. If there is a serious adverse event or an emergency unblinding event, the blind will be immediately broken.

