### Sample size calculation

Sample size estimation refers to the calculation of the required sample size in order to meet the accuracy and reliability of statistics (the control of type I errors and the guarantee of inspection efficiency) [21]. The sample size of this study was based on the relevant literature reviews and the validity of hypotheses. The main indicator of this study is to detect the difference of the total score (CMS) between the two groups before and after treatment. There is one randomized clinical trial for BSHX in the treatment of POI [13]. However, there is no placebo control group in the clinical trial and the primary outcome measurements were different. Thus, the parameters are not suitable to estimate the sample size of the trial. We referred to other clinical trials of traditional Chinese medicine in the treatment of POI patients [22]. We assumed that BSHX administration would reduce CMS score by 2.9 points and the SD is 7.42 in the study [23]. If a type I error rate of *α* = 0.05, a power of 90 % (type II error rate of *β* = 0.1), then u1 − *α* =1.64, u1 − *β* =1.28. n1 = n2 ≈ 70. During the 3-month treatment period, taking into account the possible protocol violations, and the maximum possible drop-out rate of 15%, we need 148 participants in total to achieve the number of people required for the efficacy analysis. One hundred fifty participants will be recruited for this study, and the following formula was used to estimate the sample size:
$$ n=2\times {\left[\frac{\left({z}_{1-\raisebox{1ex}{$\partial $}\!\left/ \!\raisebox{-1ex}{$2$}\right.}+{z}_{1-\beta}\right)\sigma }{\delta}\right]}^2 $$

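### Any serious adverse event breaks the blind at once, with no test of whether the allocation is needed

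*Protocol article*

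**What the plan says.** All statements are in the Methods of the protocol article unless noted.

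- **Randomization and blinding.** The commitment is that "all researchers and subjects will be blinded for the treatment allocation until the trial is completed". The next sentence is the exception: "If there is a serious adverse event or an emergency unblinding event, the blind will be immediately broken". The section does not say who learns the allocation.
- **Removal, dropout, suspension, and termination criteria.** On participant status: "Emergency unblinding or loss of eligible subjects to follow-up will be considered dropping out". On data: "If the participant drops out, the last recorded data will be recorded and analyzed". An SAE is among the listed circumstances in which "the drug treatment discontinues immediately, while safety or post-treatment visits may continue". The whole study ends if "the opening rate of emergency letters exceeds 20% of the sample size".
- **Safety assessments.** Leaving the trial after an SAE is conditional: "If a participant has a serious adverse event and was not safe to continue the trial", she is asked to withdraw. Intervention-related adverse events are monitored through records, self-report and the clinicians.
- **Sample size calculation.** "One hundred fifty participants will be recruited for this study".
- **Primary outcome, and the Abstract.** Participants complete the CMS themselves, at baseline, 3 months and 6 months.
- **Introduction.** The primary objective covers both effectiveness and safety.

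**The concern.** The trigger is worded with an or: an SAE on one side, an emergency unblinding event on the other. The SAE is thus sufficient by itself, and the requirement to act immediately leaves no step at which someone asks whether the arm needs to be known. A site following the text would open the code even for an SAE with no plausible link to the granules.

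Two things are at stake.

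1. **Safety.** It is part of the primary objective. If the code is open before relatedness is rated, knowledge of the arm can push attribution in either direction.
2. **The primary outcome.** It is self-reported, so it depends on blinding. An SAE break may either remove the woman from follow-up or leave her answering later questionnaires when she, or the person collecting them, knows the arm.

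**Working it through.** The point rests on wording, and the plan states no computed figure to reproduce. The check is a reading of the sections together, followed by arithmetic on size.

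**Step 1: is the SAE trigger unconditional?** Yes. The sentence attaches no condition of need. The Safety assessments section does attach one (whether it is safe to continue), but to withdrawal and not to unblinding.

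**Step 2: when is relatedness judged?** The article does not say. With an immediate break and no earlier recording step, the likely order is code first, relatedness second. This is an inference.

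**Step 3: what happens to her CMS data?** Two readings are open.

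| Reading | Basis | Consequence |
|---|---|---|
| The SAE break counts as emergency unblinding | Removal section: unblinding is dropping out, last recorded data analysed | A woman who could have been followed contributes a carried-forward value |
| The SAE break is separate from emergency unblinding | Removal section: drug stops, visits may go on | Later CMS scores may be unblinded, if she or the collector is told the arm |

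The or in the blinding sentence lists the two events separately, which favours the second reading. The ordinary meaning of breaking the code after an acute event favours the first. The text does not settle it.

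**Step 4: how many women?** The SAE rate p is an assumption. The expected number is 150 × p.

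- p = 2%: 150 × 0.02 = 3.
- p = 5%: 150 × 0.05 = 7.5, so about 8.
- The chance of at least one automatic break is 1 − (1 − p)^150. At 1% it is 1 − 0.99^150 = 0.78, and at 2% it is 1 − 0.98^150 = 0.95.

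**Step 5: how far could the primary comparison move?** As an illustration, take 150/2 = 75 women per arm. Suppose all 8 are in the BSHX arm and each loses the full 2.9-point reduction assumed in the sample size section. That arm's mean then moves by 8 × 2.9/75 = 0.31 points, about a tenth of 2.9. With 3 women it is 3 × 2.9/75 = 0.12. Placing all affected women in one arm is deliberately unfavourable.

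**Step 6: the termination limit.** 0.20 × 150 = 30, so exceeding it takes 31 openings (31/150 = 20.7%). If every SAE opened one letter, the binomial probability of at least 31 of 150 is:

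| Assumed SAE rate | P(at least 31 openings) |
|---|---|
| 1% to 5% | below 1e-10 |
| 10% | 0.00007 |
| 15% | 0.038 |
| 20% | 0.45 |
| 25% | 0.91 |

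**The case against.** The strongest reply is that a double-blind commitment followed by an unblinding exception is normal. The two sentences are a rule and its exception, so they do not contradict each other. That is right. What remains is that the exception is too broad, because it takes in every SAE.

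It can also be said that an article leaves SAE procedures to the full protocol and site procedures, so silence on who rates relatedness and when is no defect. That also stands, and unblinded attribution is put here only as likely. The trigger itself, however, is a stated rule and not an omission. In addition, all adverse events are to be recorded and analysed, so a plain comparison of SAE counts need not depend on relatedness ratings.

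A reader might infer three stronger points that the article does not support:

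- **That every CMS score after an SAE is unblinded.** Emergency unblinding is treated as dropping out with the last recorded data analysed, so later scores may never enter the analysis. No section says that the woman is told her arm. Some SAEs would also fall after the month-3 questionnaire.
- **That SAEs could end the trial through the 20% limit.** The article does not say that SAE breaks are made by opening emergency letters, although that is the natural reading. Even so, the limit is remote at 10% and comes into play only at SAE rates of about 15% or more.
- **That the Removal and Safety assessments sections conflict on what an SAE leads to.** One stops study drug and the other concerns leaving the trial, and both can hold. The unsettled matter is narrower: whether the unblinding that follows an SAE makes her a dropout.

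**Conclusion.** The point holds as a wording defect with a limited effect. As written, every SAE breaks the blind immediately without a test of need, which goes further than the double-blind commitment requires. Relatedness is then probably rated with the arm known. Depending on how two sections are combined, the woman becomes a dropout with a carried-forward value or stays in follow-up with CMS scores that may be unblinded.

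The size rests on an assumed SAE rate, since none is given. At 2% to 5%, about 3 to 8 of 150 women are affected. At least one automatic break is likely even at 1% (78%), so the rule would probably operate in practice. The effect on the primary comparison is probably small, and early termination through this route is not realistic at these rates. The case for changing the text is that the safety assessment is needlessly exposed and the correction is cheap.

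**What to change.** In Randomization and blinding:

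1. Remove the SAE as an automatic trigger, and allow the code to be opened only for a documented need to know the allocation.
2. Require seriousness and relatedness to be recorded before the code is opened.
3. State who may learn the allocation, and keep it from whoever collects the CMS.

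Then reconcile the Removal, Randomization and blinding, and Safety assessments sections on whether an SAE or an unblinding ends follow-up. A woman should not become a dropout with carried-forward data merely because her code was opened. The rules for stopping treatment and for terminating the study are for the sponsor and need not change on account of this point.

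The cost is a wording change and a short site memo, with no extra visits or patients. The small downside is that the investigator must document the reason for each unblinding.

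The Trial status section expected follow-up to finish by the end of November 2021. If it has finished, the report can still list each code break with its date, its reason, who learned the arm, whether relatedness was rated before or after, and which CMS scores followed it.
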